### Publications

Trial results will be communicated through manuscript publications, conference presentations, seminars, and through social media.

### Trial status

Participant recruitment started on December of 2020. At the time of manuscript submission, 251 households have been enrolled.

## Discussion

ConCorD-19 will identify whether early treatment with IFN ß1a offers a therapeutic advantage of accelerated resolution of COVID-19 and whether IFN ß1a treatment of post-exposure contacts protects from infection, thereby reducing transmission. The results from this trial may provide evidence and guidelines for a new outpatient treatment for COVID-19 with mild or moderate disease severity. Treatment interventions are needed, especially with the emergence of variants of concern that are highly transmissible, that may reduce the effectiveness of vaccinations [23].

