**Discussion:**

The results from this trial will identify whether IFN ß treatment of mild or moderate COVID-19 cases accelerates viral clearance and prevents disease progression and whether IFN ß treatment of post-exposure contacts of COVID-19 cases reduces transmission of infection.

*Trial Registration:* This trial is registered at ClinicalTrials.gov NCT04552379; date of registration September 17, 2020.

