With this strategy in mind, we have focused on the potential of post-exposure prophylaxis with interferon (IFN). Type I IFNs, IFN-αs/ß, are associated with the earliest innate immune response to viral infections. Type I IFNs invoke direct antiviral effects against different stages of viral replicative cycles and also activate immune cells to mediate viral clearance [10]. Certainly, the scientific literature is replete with evidence that pre-treatment of cells or small animals with an IFN-α or an IFN-β can protect from subsequent viral challenge. Type I IFNs were approved for therapeutic use in the context of chronic hepatitis C virus infection, in the 1990s. Notably, type I IFNs have seen limited clinical use for acute virus infections.

A clinical study that evaluated the therapeutic potential of a type I IFN against SARS, demonstrated rapid resolution of lung abnormalities in hospitalized cases treated with IFN-α [12]. More recently, results from an exploratory study undertaken in Wuhan, China, at the start of the SARS-CoV-2 pandemic, provided evidence that IFN treatment of moderate COVID-19 cases led to diminished lung pathology and accelerated viral clearance from the airways [13, 14]. Viewed altogether, the data suggest that IFN treatment for acute respiratory coronavirus infections may offer therapeutic benefits. Given the high SARS-CoV-2 transmission rates, especially with the emerging variants of concern, and the uncertainty surrounding achieving global herd immunity with vaccines, the major objective of this trial is to examine the safety and efficacy of post-exposure prophylaxis with IFN ß-1a in close contacts of confirmed COVID-19 cases. Herein we report the protocol of the Containing Coronavirus Disease 19 (ConCorD-19) study.

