### Treatment assignment and randomization

Households will be randomized as clusters to receive either IFN ß-1a treatment or standard of care, once a household meets all the inclusion and none of the exclusion criteria. Households will be randomized to IFN ß-1a treatment or standard of care at a 1:1 ratio. The minimization technique (biased coin, *p* = 0.7) will be applied to achieve balance between groups stratified by the total number of people within the household. This will be implemented through a platform provided by the Telethon Kids Institute (https://qminim.telethonkids.org.au/).

Households will be randomized during the first home visit, once eligibility is confirmed, participants have signed informed consent, and baseline data collection procedures are completed. Field team members will contact the research laboratory, at which time the household assignment to treatment or standard of care will be made by the randomization software. Participants and study staff will not be blinded to randomization of treatment or standard of care, but all data analyses will be blinded to allocation.

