### Intervention arm

Participants (index cases and treatment eligible household contacts) will receive 125 µg of pegylated IFNß-1a (PLEGRIDY®, Biogen) administered on Study Days 1, 6 and 11 (i.e. for a total of 3 doses). IFN ß-1a will be administered at the home of the participant, via subcutaneous injection from appropriately trained trial staff, for whom administration of subcutaneous injections is within their normal scope of practice (e.g. nurse or physician). The staff will remain at the home for 20 min after the last individual in a household receives their dose of IFN ß-1a, before leaving the residence, to ensure no immediate adverse events associated with IFN administration occur. All field team staff will be supplied with appropriate personal protection equipment, trained in the use of this equipment and in protocols for infection control, and will always attend in pairs. Staff administration of IFN ß-1a will ensure medication adherence.

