### Control arm

Participants randomized to the control group will receive standard of care, including symptom-based supportive treatment provided by the individual’s personal medical provider. This could include acetaminophen, non-steroidal anti-inflammatory drugs, cough suppressants, antibiotics, inhaled bronchodilators. Participants in this arm will not receive any IFN ß-1a treatment or a placebo. This standard of care approach was selected as the comparator, since no other approved intervention medications are available for non-hospitalized cases.

All participants, regardless of their allocation group, will receive a brochure with the recommendations of the Chilean Government for patients with COVID-19, including household isolation. Within each household, the index case will be asked to isolate from their contacts.

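### The article promises an answer on IFN prophylaxis of contacts, but its only contrast measures the combined effect of treating the index case and the eligible contacts

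*Protocol article*

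**What the plan says.** **The claims.** Three places in the protocol article credit an efficacy result to treating contacts.

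- Discussion: the trial will establish whether IFN "treatment of post-exposure contacts protects from infection, thereby reducing transmission".
- Abstract, Discussion paragraph: the results will show whether IFN "treatment of post-exposure contacts of COVID-19 cases reduces transmission of infection".
- Background, last paragraph: "the major objective of this trial is to examine the safety and efficacy of post-exposure prophylaxis with IFN" in close contacts of confirmed cases.

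**The design.**

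- Treatment assignment and randomization: "Households will be randomized as clusters to receive either" IFN or standard of care, 1:1, in two arms.
- Intervention arm: "Participants (index cases and treatment eligible household contacts) will receive" the drug.
- Control arm: "Participants in this arm will not receive any IFN ß-1a treatment or a placebo".
- Analysis for primary objective 2: infection in household contacts is compared between households by assigned arm.

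**The stated objective.** Co-primary objective 2 asks whether IFN lowers transmission from index cases to eligible contacts by day 11. It does not say whose treatment would produce the reduction.

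**The concern.** A contact can escape infection by two routes: the index case sheds less virus, or the contact is better protected. Under this allocation the two always change together. The trial's own rationale makes the first route plausible: the Abstract opens with the idea that interrupting shedding may lower incidence, and co-primary 1 tests whether IFN reduces shedding in index cases.

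The two readings lead to different practice. Treating diagnosed cases means one person per household. Treating exposed contacts means dosing several people who may be uninfected, with a drug that the article says causes an influenza-like syndrome in up to 80% of recipients. A positive co-primary 2, reported in the terms of the Discussion, would be taken as evidence for the second practice even if all the benefit came from the first.

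**Working it through.** **1. The plan's own figures.** These are not in dispute; the question is what they refer to.

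- Co-primary 1: 278/2 = 139 index cases per arm, 85% versus 65%, two-sided alpha 0.025. Exact Fisher power is 93.9%, in line with the stated power above 90%.
- Co-primary 2: 278 × 3 = 834 contacts, 417 per arm. Design effect = 1 + (3 − 1) × 0.15 = 1.30, so the effective number per arm is 417/1.30 ≈ 321. The control transmission rate is not given. For an odds ratio of 0.5, normal-approximation power is 80.8%, 88.2%, 92.6% and 96.7% at assumed control rates of 20%, 25%, 30% and 40%. Whatever the rate, this is power for the combined odds ratio, not for an effect of treating contacts.

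**2. Who is treated.**

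| Household type | Index case | Eligible contacts | In the trial? |
|---|---|---|---|
| IFN arm | IFN | IFN | yes |
| Control arm | none | none | yes |
| Contacts only | none | IFN | no |
| Index only | IFN | none | no |

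Attributing an effect to treating contacts needs a comparison in which the index case's treatment is held fixed. No pair of existing rows provides one. Adjusting for the index case's baseline viral load does not help, because that variable precedes treatment and cannot carry the change that treatment causes.

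**3. Illustration of what is left open.** Assume the total effect factorises into an index route and a contact route. On the odds scale, a total of 0.5 fits each of these pairs (index route / contact route) equally well: 0.5/1.0, 0.6/0.83, 0.7/0.71, 0.8/0.63, 0.9/0.56, 1.0/0.5.

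On the risk scale, with an assumed control rate p0: treated odds = 0.5 × p0/(1 − p0), converted back to a risk p1, and RR = p1/p0. If neither route is harmful, the contacts' own protection lies between 0 and 1 − RR.

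| Assumed p0 | p1 | RR | Range for contact protection |
|---|---|---|---|
| 20% | 11.1% | 0.556 | 0–44% |
| 30% | 17.6% | 0.588 | 0–41% |
| 40% | 25.0% | 0.625 | 0–38% |
| 50% | 33.3% | 0.667 | 0–33% |

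The upper limit also depends on the scale. At 30%, the fall in cumulative hazard is 1 − ln(1 − 0.176)/ln(1 − 0.30) ≈ 46%, not 41%. The lower limit stays at zero in every row, and that is the substance of the point.

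**4. Whether the untreated contacts rescue the claim.** Treatment-ineligible contacts are enrolled and receive no IFN in either arm. With an assumed 0.25 to 1 per household (about 35 to 139 per arm), a 30% control rate and an odds ratio of 0.5, power at alpha 0.025 is about 15% to 57%, before any allowance for clustering. They also differ from eligible contacts by age or contraindication, and they may benefit when other eligible contacts in the household are treated. Such a comparison would not isolate the index route.

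**The case against.** The strongest reply is that the operative plan is sound. Objective 2 concerns transmission within households, the analysis compares households by arm, and the Study overview states openly that index cases and contacts are both treated. Treating the whole household is a deliberate strategy, and the randomised comparison estimates its effect validly. All of this stands. A reader might infer that co-primary 2 is invalid or unanswerable, or that the trial needs another arm; the documents do not support either reading. No hypothesis, estimate or sample size changes.

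A reader might also infer that the trial can say nothing about giving IFN to contacts. That goes too far. The Background sentence covers safety as well as efficacy, safety in prevention is a listed secondary objective, and adverse events in contacts can be compared between arms.

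Third, the range of 0–41% could be mistaken for a bound on the prophylaxis effect. It is not one. It needs an assumed control rate, a multiplicative split, no harm by either route, and an observed effect equal to the planning value.

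Finally, ineligible contacts are enrolled expressly to study transmission in the household, secondary objective 2 is not limited to eligible contacts, and the statistical analysis plan, which is not shown, may contain an analysis of them. So the absence of that analysis from the article is no fault. No analysis plan can supply the missing contrast, though, and the over-attribution is printed in this article.

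**Conclusion.** The point holds as a fault in the stated efficacy conclusion, not in the design or in Objective 2. Three passages promise an effect of treating contacts; the trial can deliver only the total effect of treating the index case and all eligible contacts together. This follows from the allocation alone and needs no assumption about rates or models.

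The split between the routes is not identified at any sample size. A total odds ratio of 0.5 is compatible with no benefit at all from treating contacts. The numerical ranges above only illustrate this. Success on co-primary 1 would make attribution to prophylaxis harder, because it would support the competing route.

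**What to change.** 1. In the Abstract's Discussion paragraph, the last paragraph of the Background and the Discussion, reword the efficacy statements as the combined household-level effect of treating the index case and all eligible contacts. Interpret co-primary 2 in the same terms, and do not attribute it to prophylaxis of contacts.
2. Keep Objective 2 as it is, adding only a note that both roles are treated in the IFN arm. Keep the safety evaluation in contacts.
3. Optionally, report the between-arm comparison in treatment-ineligible contacts as an exploratory, imprecise estimate of indirect protection from treating other household members, not of the index route alone. First confirm that RT-PCR or serology outcomes exist for them: the biospecimen section names only index cases and eligible contacts for sampling.

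Items 1 and 2 cost a few sentences and a less far-reaching claim. They should be made before results are known. The cost of item 3 depends on whether samples were taken. With 251 of 310 households already enrolled at submission, samples not collected from those households are unlikely to be recoverable.

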## Data Availability

Not applicable.

## Abbreviations

AE: Adverse events
COVID-19: Coronavirus Disease 19
DSMB: Data and Safety Monitoring Board
IFN: Interferon
MERS: Middle East respiratory Syndrome
MS: Multiple sclerosis
RT-PCR: Real-time Polymerase Chain Reaction
REDCap: Research Electronic Data Capture
SAE: Serious adverse event
SARS: Severe Acute Respiratory Syndrome
